## Abstract

**Background:**

Adherence to antiretroviral medications is a key determinant of clinical outcomes. Many adherence intervention trials investigated the effects of time-intensive or costly interventions that are not feasible in most clinical care settings.

**Objective:**

We set out to evaluate a collaborative care approach as a feasible intervention applicable to patients in clinical care including those with mental illness and/or substance use issues.

**Methods:**

We developed a randomized controlled trial (RCT) investigating an integrated, clinic-based care management approach to improve clinical outcomes that could be integrated into the clinical care setting. This is based on the routine integration and systematic follow-up of a clinical assessment of patient-reported outcomes targeting adherence, depression, and substance use, and adapts previously developed and tested care management approaches. The primary health coach or care management role is provided by clinic case managers allowing the intervention to be generalized to other human immunodeficiency virus (HIV) clinics that have case managers. We used a stepped-care approach to target interventions to those at greatest need who are most likely to benefit rather than to everyone to maintain feasibility in a busy clinical care setting.

**Results:**

The National Institutes of Health funded this study and had no role in study design, data collection, or decisions regarding whether or not to submit manuscripts for publication. This trial is currently underway, enrollment was completed in 2015, and follow-up time still accruing. First results are expected to be ready for publication in early 2017.

**Discussion:**

This paper describes the protocol for an ongoing clinical trial including the design and the rationale for key methodological decisions. There is a need to identify best practices for implementing evidence-based collaborative care models that are effective and feasible in clinical care. Adherence efficacy trials have not led to sufficient improvements, and there remains little guidance regarding how adherence interventions should be implemented into clinical care. By focusing on improving adherence within care settings using existing staff, routine assessment of key domains, such as depression, adherence, and substance use, and feasible interventions, we propose to evaluate this innovative way to improve clinical outcomes.

**Trial Registration:**

Clinicaltrials.gov NCT01505660; http://clinicaltrials.gov/ct2/show/NCT01505660 (Archived by WebCite at http://www.webcitation/ 6ktOq6Xj7)

## Introduction

Adherence to antiretroviral medications (ARVs) is a key determinant of outcomes including viral suppression and prevention of disease progression and death [1-9]. Unfortunately, poor adherence among persons living with human immunodeficiency virus (HIV/PLWH) is common with mean levels of adherence in clinical cohorts often 60% to 80% or less [3,10-13]. Substance use and mental illnesses such as depression are key predictors of poor adherence [3,10,14-36], common among PLWH [20,36-41] and may be crucial to identify and treat among those with poor adherence [42].

The importance of translating research on improving adherence into clinical practice has been noted [43]. Previous studies investigating a variety of adherence interventions have reported benefits, although often small [44-46]. Many focused on testing a single device, such as a pager or other electronic reminder system, or investigated the effects of time-intensive costly interventions that are not feasible in most clinical settings, and therefore failed to inform adherence in clinical care [44].

We sought to evaluate a collaborative care approach as a feasible intervention applicable to PLWH in care, including those with mental illness and substance use. Collaborative care approaches are multimodal interventions that typically involve a care manager who helps develop a shared definition of a problem, sets goals, develops specific action plans, offers problem solving and support, and facilitates appointments [47]. These interventions have shown value for people with depression and anxiety, heart failure, and chronically ill seniors [47-62]. While there is little experience with care management approaches among PLWH particularly as related to adherence, treatment of depression is an exception [63]. Many studies of care management models have been conducted as off-site studies separate from clinic settings, have incorporated extensive additional clinical research staff, or have included time-intensive interventions such as community outreach with home visits that may not be feasible to implement on a broad scale in clinical care [49-51,63].

We developed a randomized controlled trial (RCT) investigating an integrated clinic-based care management approach to improve outcomes. This approach is based on routine integration and systematic follow-up of a clinical assessment of patient-reported outcomes (PROs) targeting domains, including adherence, depression, and substance use, and adapts the previously tested care management approach used in the Program to Encourage Active, Rewarding Lives (PEARLS) study [50]. The health coach or care management role is provided by clinic case managers allowing the intervention to be generalizable to other HIV clinics with case managers. We hypothesize that our care management intervention will improve adherence compared with usual care. This paper describes the trial design and rationale for key methodological decisions.

## Methods

### Description of Trial and Intervention

#### Overview

We integrated a RCT into clinical care of PLWH. PLWH who reported inadequate adherence on the clinical assessment of PROs that is already being completed as part of routine clinical care visits were eligible for the RCT. Case managers in the clinic serve as the care managers for the intervention arm of the study. They are already part of the clinic and available to help PLWH when requested. However, in addition to these services, those in the intervention arm received a more structured and scheduled care management intervention, that included scheduled assessments and follow-up, a stepped-care approach, and, if needed, more intensive intervention such as problem solving therapy. A key difference between the intervention and usual care arms is that the case managers receive automatic email reminders of the need to follow-up with the patient at set intervals and conduct specific assessments facilitating a more systematic approach rather than ad hoc support.

#### Design

This prospective RCT is integrated into clinical care of PLWH at the University of Washington (UW) Harborview Madison HIV clinic (hereinafter “the UW HIV clinic”). Eligible patients are randomized to either a usual care arm or an intervention/enhanced support arm with a 1:1 ratio without blocking or stratification using a computer-based random number generator. Results of the randomization are applied to the database and tracking platform by a research coordinator who oversees the computer-based number generator and is not involved in enrollment and consent and has not met the participants. Patients are followed for 12 months as part of the trial.

#### Setting

The UW HIV clinic is the largest single provider of medical care to PLWH in the northwestern United States and provides care to approximately 2800 PLWH. The clinic provides primary care, on-site specialty care, financial and case management, and pharmacy services.

#### Clinical Assessment

We developed and implemented a clinical assessment platform for routine collection of PROs in clinical care, including instruments that measure medication adherence, drug and alcohol use, sexual risk behavior, and depression and anxiety symptoms [64-68]. Examples of instruments collected as part of the clinical assessment include the 9-item Patient’s Health Questionnaire (PHQ-9) measure of depression symptoms [69,70], medication adherence (several items with varying recall periods) [71,72], and substance use (Alcohol Use Disorders Identification Test Consumption Items and Alcohol, Smoking, and Substance Involvement Screening Test) [73-76]. We obtained input from outside clinical technology experts and conducted time-and-motion studies and qualitative semistructured interviews from key informants including patients, providers, and staff members to ensure implementation was not disruptive and inform the content of the assessment [65]. A primary goal was to ensure that the clinical assessment was completed on the day of and prior to provider visits to ensure that assessment feedback was available to providers at the time of the visit [77]. Patients at the UW HIV clinic complete the assessment every 4 to 6 months and assessment feedback is given to providers and case managers as a now established part of clinical care. This occurs for all patients regardless of whether or not they are in this trial.

#### Participants

Participants are 18 years of age or older, English-speaking PLWH with inadequate ARV adherence as measured by self-report using a single item on the clinical assessment given to all patient at Madison clinic asking about the number of missed doses during the prior 14 days. Eligible patients have access to either a home or cellphone and are in care at the UW HIV clinic for at least 6 months. Patients are ineligible if they are severely cognitively impaired or actively psychotic as these patients are not asked to complete the clinical assessment. To enhance generalizability and relevance to a broad spectrum of patients in routine care, patients are not excluded based on substance use or depression.

#### Intervention

The intervention uses a care management approach that is incorporated into clinical care settings and has previously been shown to be useful in the care of patients with diabetes and epilepsy and more effective than providing PRO feedback alone [47,50,51,54]. Case managers are tasked with providing patient education and support, working with patients to develop a shared focus on specific problems with targeted goals and specific action plans. Our choice to incorporate case managers in this intervention allows them to focus on health domains case managers consider important, including adherence, depression, and substance use.

Case managers are available for patient or case manager-initiated interactions in both the usual care and intervention arms and each case manager has patients in both arms. In addition, the intervention arm uses automated email reminders for case managers to facilitate a more systematic approach targeting those who need it most. All patients in the intervention arm receive a structured 10 to 15 minute follow-up telephone call from their case manager 2 and 6 to 8 weeks after enrollment. A brief assessment including the depression, medication adherence, and substance use instruments from the clinical assessment that is given to all patients as part of clinical care visits is administered at the beginning of each call. Case managers then provide education and support based on responses, working with patients to develop targeted goals and plans. After a second call, a stepped-care approach is used for those patients identified as needing more intensive interventions (Figure 1).

Patients in the intervention arm who continue to report inadequate adherence after 6 weeks receive a more intensive intervention based on the PEARLS approach, which includes (1) problem solving therapy, (2) social and physical activation, (3) pleasant events scheduling, and (4) patient support and education regarding ARV use. We modified this approach to facilitate clinical care integration and to accommodate daily experiences of PLWH. For example, we modified the list of possible pleasant events and activities taking into account the limited incomes of many patients. Motivational interviewing techniques are used to facilitate substance use reduction.

Problem solving therapy (PST) involves up to 6, approximately 40-minute sessions with the case manager over 6 months, typically in-person at the clinic. PST is a skills-enhancing behavioral treatment based on the assumption that the accumulation of problems in living cause and promote inadequate adherence (and other maladaptive behaviors and symptoms). PST is a skill-building method consistent with modern self-management support strategies used in managing chronic medical illness [78]. PST helps to define and clarify problems and provides a structured, realistic, and achievable approach to solve problems and meet individual goals. Everyone in the intervention arm including those doing well with adherence early on also receive follow-up “check-in” calls by the care manager with a brief assessment at approximately 9 and 12 months after enrollment.

**Figure 1 figure1:**
[figure not shown]
Participant flow including eligibility, enrollment, and follow-up. PRO: patient-reported outcomes.

#### Training

Case managers received a 2-day training session at the beginning of the trial focused on motivational interviewing techniques and PST led by an HIV specialist, psychiatrists, and psychologists with expertise in training for PST and motivational interviewing. An intervention manual based on IMPACT, PATHWAYS, and PEARL collaborative care trials formed the basis of training on collaborative care, stepped-care principles, and PST [50,55,57]. Training included didactics, role-playing exercises, group discussion of the role-play activities, and observation of a videotaped demonstration. We have also done 1 booster session to date and record a small subset of sessions looking for a means of improvement.

#### Platform

One goal was to use the PRO platform to promote practice system changes to improve outcomes by facilitating systematic monitoring and follow-up, proactive care management, and information sharing with the entire team. Based on this goal, we used the open-source PRO platform [79] already integrated into the clinic to collect the clinical assessment and used for similar work in oncology and other clinics [64,66,80-84]. The platform notifies team members by pager when a patient’s clinical assessment results suggest trial eligibility. Once enrolled and assigned to the intervention, the platform sends automatic email notifications to individual care managers when their patients are due for a call or PST session, tracks attempted and completed calls, and sends automatic reminders if calls or PST sessions are not completed. Care managers can use the platform to conduct brief phone-based assessments with patients at the beginning of follow-up calls. The platform incorporates skip patterns and eliminates paper-based forms. Finally, the platform facilitates rapid integration of care manager documentation including assessment results that can be directly entered into the UW HIV clinic’s electronic health records (EHR) to notify other health care team members as needed. The platform reduces research coordination time for the trial and promotes the feasibility of the intervention in clinical care and further provides an easy way to track intervention fidelity in terms of care manager completion rates.

#### Outcomes

The primary trial outcome is change in adherence as measured by the clinical assessment, however changes in depression symptom severity is also important. Standard PHQ-9 scores range from 0 to 27 and are categorized as: none (0-4 points), mild (5-9 points), moderate (10-14 points), moderately-severe (15-19), and severe (≥20 points) depressive symptom severity [70]. PHQ-9 standard scores have curvilinear measurement properties with respect to the latent trait of depression defined by all the items, meaning that a constant difference in score implies different amounts of depression symptom severity at different depression severity levels [85]. In this situation, using continuous standard total scores in regressions can lead to confusing and even biased findings [86]. We therefore will generate scores using item response theory (IRT) as done previously [85]. IRT-based depression severity scores have linear scaling properties with respect to the latent trait of depression defined by all the items [87]. These outcomes are based on clinical assessments integrated into routine care for all clinic patients and measured every 4 to 6 months, and do not include study specific measures. While using data from clinical care requires greater flexibility in terms of outcome timeframe windows, it allows data collection for primary outcomes to be completely distinct and independent of whether a patient was in the intervention or the usual care control arm.

Important secondary outcomes include antidepressant medication use, HIV-1 viral load (VL), alcohol and substance use, health-related quality of life, and symptom burden. Medications including antidepressant medication are collected as part of the EHR. Even medications filled by other pharmacies are captured because all prescriptions from the clinic are written within the EHR and then sent via the EHR to the correct pharmacy allowing a very high capture of medications including initiating a new antidepressant medication or increasing a dose of an existing antidepressant medication. VL values are measured as part of routine clinical care, and therefore timing varies. Cut-offs of <40 are considered undetectable although we also tend to repeat VL analyses using a cut-off of <400 to exclude viral blips. Health-related quality of life, symptom burden, and current drug and alcohol use are captured through the clinical assessment.

In addition, we will examine process outcomes, including provider diagnoses (depression, substance use) and referrals and visits with mental health counselors, substance use counselors, and health educators. Diagnoses including drug and alcohol use are captured in the EHR as is information regarding scheduled, kept, and cancelled visits as well as visit types. These outcomes are collected as part of routine care.

#### Incentives

There is no incentive for completing the clinical assessment as this is part of clinical care for all patients. Despite this, refusal rates have been low to date; the current refusal rate is 1%. There are no financial incentives for participating in this trial as the trial philosophy is assessing the impact of systematic approaches to care management to improve clinical care. Bus passes are available for participants who meet with their care manager on a day when they otherwise would not be in clinic.

#### Statistical Analyses

Clinical data will be used to assess differences between patients enrolled in the trial and eligible patients not enrolled. Primary analyses comparing outcomes in the usual care versus intervention arms will be performed on an intent-to-treat basis focused on 1 year after enrollment. Secondary analyses will be done on an as-treated basis with censoring if patients do not complete follow-up. We have previously found missing rates of <4% for clinical assessment items [64] but will use multiple imputation approaches to address this if necessary. Descriptive analyses compare patients in the intervention and usual care arms on demographic and clinical variables, including depression status, adherence, substance abuse, use of mental health services, and use of antidepressant medications to assess whether groups are balanced at baseline. Depending on the distribution, we will likely use linear mixed-effects models [88,89] to assess differences in adherence levels taking into account within-subject correlations between adherence levels over time and the influence of potential confounding covariates. We will look for influential outliers in the regression model and we will explore nonlinear transformations of the outcome measure to see if the linearity assumption is violated. We will check an unstructured version of the working correlation matrix to ensure that our default working correlation, exchangeable, is properly specified. Selection of variables for inclusion in the models will be based on likely confounding factors based on the literature to date, coupled with inclusion of variables observed to be strong risk factors for the outcome and are therefore potential “precision variables” to improve statistical efficiency. Model fit will be assessed with *R*^2^, we will report the ratio between the variance that is accounted for by the random effects and the residual variance, and we will determine whether the linear mixed-model’s distributional assumptions are met [90]. We will examine effect modification of the pattern of change in adherence over time between groups by depression and substance abuse status. We will also examine baseline characteristics as potential moderators of intervention effects [91,92]. We will compare loss-to-follow-up rates in the 2 groups. If these rates exceed 5% or differ between groups, we will use baseline assessment data and clinical information data to assess for potential bias. Sensitivity analyses will be conducted to determine the impact of dropout [93,94] and spillover effects and to evaluate additional longer timeframes. We will examine the impact of the intervention on visit frequency with case managers in both the intervention and usual care arms looking for potential spillover effects of the intervention on the usual care arm. Our last sensitivity analysis will be an “as treated” analysis, using inverse probability of treatment weights. This will account for the possibility of differential switching between groups (ie, drop out) as a form of contamination and can assist in the interpretation of the primary endpoint. However, we intend to use the intention to treat analysis as the primary study endpoint, as we see the benefits of randomization for confounder control as exceeding the risks of validity posed by contamination. We thus follow recommendations of a Cochrane review: randomized design, follow patients for >5 months, analyze patients in the groups to which they were randomized, and control for baseline values or use differences between follow-up and baseline values as the main outcome [95].

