
#### Sample Size

We based sample size estimates on a two-tailed significance level (alpha) of .05 and power (1-beta) of .80 [96]. With 115 individuals in each arm (N=230), we would be able to detect even a 4% increase in adherence in the intervention arm. We expect a loss to follow-up rate between 8% and 10%, but conservatively account for a 15% loss to follow-up rate and increased our overall sample size target to 270. Power for this type of trial should be sufficient to identify small to moderate effects [97] (defined as effect sizes of 0.2-0.5 [98]). Even if we have a higher than expected loss to follow-up rate of 15%, we will have sufficient power to detect effect sizes of 0.35, well within the small-to-moderate effects continuum and in line with the magnitude of effects seen in other adherence intervention studies [44,99,100]. We expect several of our outcomes will be more responsive to change than overall adherence particularly many of the binary process outcomes. We will have more than sufficient power to detect differences in those outcomes. While we plan to attempt to enroll 270 individuals, one of the outcomes of interest is the willingness of patients to participate in these types of interventions. Therefore, we are also specifically interested in whether it is feasible to enroll this many individuals from a clinical care setting in a reasonable amount of time.

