### Adherence Measurement

Patients with inadequate medication adherence measured by the 14-day adherence item are eligible for inclusion. Although self-reported adherence has been critiqued for inaccuracies, these concerns have centered on over-reporting rather than under-reporting of adherence. Patients who report poor adherence are likely to truly have poor adherence. We chose the 14-day timeframe to include weekends, which are frequent times of missed doses and avoided longer time frames to limit recall errors and focus on current behavior.

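### The plan allows a change-score primary analysis, which is never more precise than adjusting for baseline, and states no consequence if its exchangeable default fails the planned check

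*Protocol article*

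**What the plan says.** The Outcomes section states: "The primary trial outcome is change in adherence as measured by the clinical assessment". The Statistical Analyses section sets the primary comparison as intention-to-treat, centred on one year. It says the likely model is a linear mixed model of adherence levels over time, with covariates chosen partly to improve precision. It closes by following a cited Cochrane review whose advice includes to "control for baseline values or use differences between follow-up and baseline values as the main outcome". It does not say which of the two is primary.

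On correlation, the same section plans to compare an unstructured matrix with the default, to make sure that "our default working correlation, exchangeable, is properly specified". It gives no action if the comparison fails and mentions no robust standard errors.

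On eligibility, the Adherence Measurement section says: "Patients with inadequate medication adherence measured by the 14-day adherence item are eligible for inclusion". So the 14-day value at entry is known for every participant. The Outcomes section does not name the item used for the primary outcome; I take it to be the same 14-day item.

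**The concern.** A difference from baseline and a baseline-adjusted comparison are both unbiased in a randomised trial, but they do not have the same variance. Offering them as equals, with the outcome worded as change, leaves the less efficient one available as the primary analysis. It also leaves the choice between them open. What is at stake is power, lost for no saving because the baseline value is already in hand.

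The mixed model of levels does not settle the matter. If baseline enters as one of the outcomes with a free mean in each arm, the arm-by-time contrast at 12 months is, with complete data, the change-score difference. The loss is avoided only if baseline is a covariate, or if the arms are constrained to be equal at baseline.

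The default correlation matters for that same contrast. The standard error of a baseline to 12-month change depends directly on the correlation between those two occasions, and an exchangeable structure replaces it with an average over all pairs of visits.

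**Working it through.** **The plan's own figures.** The Sample Size section uses a "two-tailed significance level (alpha) of .05 and power (1-beta) of .80" and 115 per arm. The detectable standardised effect is (1.960 + 0.842) × √(2/115) = 0.37. Four percentage points at that effect imply an SD of 4/0.3695 = 10.8 points; the article does not state an SD, or whether it would be of level or of change. Enrolment: 230/0.85 = 271, against the stated 270. The stated effect size of 0.35 is not reproduced at 115 per arm (power 75.6%; 129 per arm would be needed). That is a separate matter and is not used below.

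**Precision.** Assumptions: follow-up SD = 1, baseline SD = q, within-trial correlation r. Neither q nor r is in the document.

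- Var(change) = 1 + q² − 2rq
- Var(adjusted) = 1 − r²
- Difference = (q − r)², which is never negative. The change score can therefore equal the adjusted analysis (when r = q) but never beat it.

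Power for 4 points at 115 per arm, taking 10.8 as the follow-up SD, is Φ(2.80/√V − 1.96), where V is the relevant variance.

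| q | r | V change | V adjusted | Ratio | Power, change | Power, adjusted |
|---|---|---|---|---|---|---|
| 1.0 | 0.2 | 1.60 | 0.96 | 1.67 | 60.1% | 81.6% |
| 1.0 | 0.3 | 1.40 | 0.91 | 1.54 | 65.8% | 83.6% |
| 1.0 | 0.5 | 1.00 | 0.75 | 1.33 | 80.0% | 89.9% |
| 1.0 | 0.7 | 0.60 | 0.51 | 1.18 | 95.1% | 97.5% |
| 0.7 | 0.2 | 1.21 | 0.96 | 1.26 | 72.1% | 81.6% |
| 0.7 | 0.3 | 1.07 | 0.91 | 1.18 | 77.3% | 83.6% |
| 0.7 | 0.5 | 0.79 | 0.75 | 1.05 | 88.3% | 89.9% |
| 0.7 | 0.7 | 0.51 | 0.51 | 1.00 | 97.5% | 97.5% |

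If baseline spread instead exceeds follow-up spread, as a ceiling-bounded item could produce, the ratio at q = 1.3 is 2.26 (r = 0.2) to 1.71 (r = 0.7).

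**Effect of selecting on low baseline.** Bivariate normal data were simulated and truncated to the lowest 20% or 40% of baseline. At a parent correlation of 0.5 the variance ratio falls from 1.33 to 1.07 and 1.10. At 0.3 it falls from 1.54 to 1.12 and 1.17. Truncation narrows the baseline spread (q about 0.5 to 0.6 in these runs), and that reduces the penalty.

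**Exchangeable default.** Assumption: correlation decays geometrically with time. The exchangeable value is the mean of the pairwise correlations, and for the 12-month change

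SE(model)/SE(true) = √[(1 − r_exch)/(1 − r_0,12)].

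Take assessments at 0, 4, 8 and 12 months with a 0 to 12-month correlation of 0.3. Adjacent correlation is 0.3^(1/3) = 0.67, and r_exch = (3 × 0.669 + 2 × 0.448 + 0.3)/6 = 0.534. The ratio is √(0.466/0.70) = 0.82, and type I error is 2[1 − Φ(1.96 × 0.816)] = 11.0%. In 400 simulated trials with a random-intercept model, the mean SE was 0.127 against an empirical SD of 0.160, with 12% rejections.

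Over 0 to 12-month correlations of 0.1 to 0.5:

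- 4 assessments: SE ratio 0.87 to 0.79, type I error 8.9% to 12.3%
- 3 assessments: SE ratio 0.92 to 0.85, type I error 7.2% to 9.5%

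Both schedules fit the routine interval of 4 to 6 months.

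**The case against.** Four points deserve weight.

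- **The plan does not commit to a change score.** A reader might infer that it does, from the wording of the primary outcome. But baseline control is listed first, the likely model is of levels, and baseline adherence is an obvious candidate among the precision covariates. Moreover, once baseline is a covariate, analysing change or level gives the same treatment effect. This stands: the fault is that the less efficient option is allowed, not that it is chosen.
- **Selection on low baseline does not create the loss.** A reader might infer this because eligibility and outcome appear to rest on the same noisy item. Simple truncation shrinks the penalty, as shown above. The regression to the mean that selection produces falls on both arms alike in expectation, so it does not bias the comparison. This stands in full.
- **An inflated error rate is not planned.** A reader might take 11% or 12% as what the trial will have. The same sentence that names exchangeable as default also plans a check against an unstructured matrix, and the inflation needs decaying correlation, model-based standard errors and no action after the check. What remains is that no action is stated.
- **Detail may sit in a fuller plan.** Visit windows, the fallback covariance and the degrees-of-freedom method properly belong in an analysis plan that is not shown. That is fair for those items. It does not cover what the article itself states: an outcome worded as change, and two unequal estimators presented as equivalent.

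**Conclusion.** The point holds as one of efficiency. The article allows a primary analysis that cannot be more precise than the available alternative and may be appreciably less so. The variance ratio is about 1.2 to 1.7 with equal spread and r from 0.7 to 0.2, and about 1.0 to 1.3 if baseline spread is 0.7 of follow-up spread. At r = 0.3 that is 66% or 77% power for 4 points, against 84% with adjustment. Because selection may well have narrowed the baseline spread, the lower range should not be dismissed, and the loss could be close to nil. SD, correlation and spread ratio are all assumed; the power figures also rest on the back-calculated SD of 10.8 being that of follow-up level.

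The covariance point is secondary and conditional. If correlation decays with time and the default is kept, the standard error of a 12-month change is understated by about 8% to 21%, with type I error about 7% to 12%. The planned check may prevent this, but the article does not say how.

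Neither part makes a correctly executed randomised comparison biased.

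**What to change.** - In Outcomes and Statistical Analyses, define the primary contrast as the difference between arms in 14-day adherence at 12 months, from a model with baseline 14-day adherence as a covariate, or with the arms constrained equal at baseline.
- Delete the option of using differences from baseline as the main outcome.
- Make an unstructured covariance over defined visit windows, or robust standard errors, the default. If exchangeable is kept as a starting point, state what will be used when the check shows a difference.

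The cost is wording only: no added patients, visits or data. The one small downside is that routine-care assessments fall at irregular times and must be grouped into windows if an unstructured covariance is used. Robust standard errors avoid that.
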